### Ethical Considerations

The trial was approved by the Committee on Research Ethics in Psychology at Vilnius University on November 13, 2023, no. 21/(1.13 E) 250000-KT-166 Vilnius. All participants will be informed about the study conditions and will have to sign an informed consent form before participating in the study.

Informed consent will be collected using an online form before starting the initial screening. Additional written informed consent to participate in the intervention will be obtained face-to-face before the beginning of the VR exposure sessions by the researcher conducting the session. Participants will provide their contact information—email and telephone number—which will be stored in a secure server that will be available to access only to the research team after logging in to the platform. Each participant will have a generated ID number that will be used for appointment scheduling and as a stable identifier in the database across measurements. Signed informed consent forms that also include the name of the participant and contact information will be stored in a locked safe that can only be accessed by one of the team members.

The day-to-day operations will be overseen by the principal investigator with the support of the Lithuanian research team. The trial will receive regular and need-based support from Swedish and Belgian researchers who have vast experience in online-based interventions and VR applications for treating various psychological issues. In case of a need for major changes in the trial protocol, these changes will be reviewed and approved by the institution’s Research Ethics Committee before being implemented. No separate data monitoring committee will be appointed in this study. Participants’ experiences and fidelity to the protocol in the course of face-to-face sessions will be discussed weekly and reported by therapists performing the sessions during the supervision meetings. During the online intervention, participants will be instructed to contact the program’s therapists in case of a deteriorating psychological condition. During the period of data collection, the principal investigator will meet weekly with the research team and the therapists to review the progress and discuss any issues.

Participants will be instructed to reach out via the online intervention platform or other means to the research team in case they experience adverse effects or a worsening of psychological state after the face-to-face session or during the online intervention program. All incidents of adverse effects will be reported.

## Results

### Recruitment

The recruitment to the study officially started in January 2024. As of November 2025, a total of 101 participants have completed the initial screening, of whom 37 met the inclusion criteria and were randomized. Recruitment of participants was still ongoing during the submission of this paper in December 2025. The final results of the study are expected to be prepared and submitted for publication in March 2026.

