**Methods:**

This randomized controlled trial will aim to recruit 86 higher education students experiencing high levels of public speaking anxiety, who will be randomized into one of two conditions: either 1 or 3 sessions of VR exposure therapy, with the same total number of exposure exercises. Both conditions will be followed by the same 4-week online program to encourage in vivo exposure tasks for both conditions. The study will be an exploratory superiority trial testing whether one of the conditions is superior to the other. The primary outcome will be the Public Speaking Anxiety Scale. Assessments will take place pretreatment, at the beginning of the face-to-face session, during the face-to-face session, 1 week after the last VR exposure session, at the end of 4 weeks of the online program, and at two follow-ups at 3 and 12 months after finishing the online program, or equivalent time if the online program was discontinued. Repeated measures within-between ANOVA, the reliable change index (RCI), and effect sizes will be used as statistical analyses, and intention-to-treat will be the primary analysis approach; additional per-protocol analysis will be reported.

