### Sample Size

Sample size was calculated for superiority analysis to test whether one condition shows bigger effects at least at the medium effect level. Power analysis was performed using the G*Power program for repeated measures ANOVA between factors’ effects, which showed that given a significance level of .05 to achieve 80% power to detect a medium between-groups effect (Cohen *f*=0.25) with 2 groups × 3 time measurements (pretreatment, 1 week post last exposure session, and at the end of the online intervention period or equivalent time), with an estimated correlation between repeated factors of 0.5, a total sample of 86 is needed.

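### With 37 randomised after about 22 months and results due in March 2026, the planned 86 and its 80% power are very unlikely to be reached, and the article does not say so

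*Protocol article*

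**What the plan says.** The abstract (Methods) gives the target: "This randomized controlled trial will aim to recruit 86 higher education students". The Sample Size section derives it from a G*Power calculation for the between-factors effect of a repeated measures ANOVA, with two groups, three measurements, a correlation of 0.5 and f = 0.25. It concludes, "given a significance level of .05 to achieve 80% power", that "a total sample of 86 is needed".

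The Recruitment section under Results dates the start of recruitment to January 2024. As of November 2025, 101 people had completed screening, "of whom 37 met the inclusion criteria and were randomized". Recruitment was still open in December 2025. The section adds: "The final results of the study are expected to be prepared and submitted for publication in March 2026".

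The abstract's Results paragraph gives the 101 screened and the March 2026 date, but not the 37. The version history dates the current version to 3 July 2026. The abstract's Conclusions and the Discussion call the sample small or limited and ask for confirmation in larger samples. No section changes the target, says that it will be missed, or gives power at a smaller number.

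**The concern.** The target, the count and the reporting date stand in one document and do not fit together. The power statement describes a trial of 86, while the timeline describes one of roughly half that size.

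The trial asks a two-sided superiority question, and the Introduction and Interventions sections cite a meta-analysis that found no difference between one and several sessions of in vivo exposure. If the comparison here is non-significant, a reader who believes the study had 80% power for a medium effect may take the result as evidence that the two formats work equally well. At the sizes the timeline allows, the data could not support that.

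The abstract adds to the difficulty: a target of 86 next to 101 screened can look like a target that has been met.

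**Working it through.** **Inputs from the protocol article.** Sample Size: N = 86, alpha = 0.05, power 80%, f = 0.25, 2 groups, m = 3 measurements, rho = 0.5, no dropout allowance stated. Recruitment: start January 2024; 37 randomised as of November 2025; results expected March 2026.

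**1. Reproduce the planned figure.** For the between-factors effect the noncentrality is lambda = f² × N × m / (1 + (m − 1) × rho), with 1 and N − 2 degrees of freedom. Here that is 0.0625 × N × 3 / 2 = 0.09375 × N. At N = 86, lambda = 8.06 and power is 0.801. No smaller N reaches 0.80, so 86 reproduces exactly.

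**2. Accrual rate.** The exact days are not given, so the window is 21 months (end of January 2024 to start of November 2025) to 23 months (start of January 2024 to end of November 2025).
- 37 / 21 = 1.76 per month; 37 / 23 = 1.61 per month.
- Still needed: 86 − 37 = 49. Time at these rates: 49 / 1.76 = 27.8 months; 49 / 1.61 = 30.5 months.
- By the end of March 2026: 37 + 4 × 1.61 = 43.4, or 37 + 5 × 1.76 = 45.8. That is about 43 to 46.
- To reach 86 by then would take 49 / 5 = 9.8 to 49 / 4 = 12.3 per month, roughly six to eight times the observed rate.
- If recruitment ran on to July 2026, the date of the current version, eight further months would give about 50 to 51.

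The usable cut-off is earlier than the reporting date, because the assessment after the online programme falls at least five weeks after the last VR session.

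**3. Power and precision at the attainable sizes.** Power and detectable f use the formula in step 1. The half-width is for a baseline-adjusted difference at t2 in SD units: t(0.975, N − 3) × sqrt(4/N × (1 − rho²)), with rho = 0.5 and equal arms. This baseline-adjusted model is an assumption made here, not the protocol's stated analysis.

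| N | lambda | Power at f = 0.25 | f detectable at 80% | 95% CI half-width (SD) |
|---|---|---|---|---|
| 86 | 8.06 | 0.80 | 0.25 | 0.37 |
| 37 | 3.47 | 0.44 | 0.39 | 0.58 |
| 43 | 4.03 | 0.50 | 0.357 | 0.53 |
| 46 | 4.31 | 0.53 | 0.345 | 0.52 |

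Example at N = 43: 2.021 × sqrt(4/43 × 0.75) = 2.021 × 0.264 = 0.53. At N = 50 to 51, power is 0.56 to 0.57.

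An estimate near zero at N = 37 to 46 would therefore have an interval reaching beyond 0.5 SD in both directions. All figures assume no dropout.

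**The case against.** The strongest reply is that nothing in the Sample Size section is wrong. The 86 is an a priori figure, it reproduces, and slow accrual does not falsify it. That stands: the figure should remain on record as the planned size. A reader might infer that the calculation was faulty or should be overwritten, and the document gives no support for that.

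A second reply is that the final number is unknown. Recruitment was open in December 2025, no closing date is given, and the March 2026 date had already passed when the current version was issued. This also stands. One cannot say as fact that the realised trial has half its planned size. The projection is robust all the same: even recruiting to July 2026 at the observed rate gives only about 50.

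Third, one might conclude that a non-significant result is the likely outcome even if a true medium effect exists. By the protocol's own formula it is about an even chance at 43 to 46, and more likely than not only at the lower counts.

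Fourth, one might say that the abstract hides the shortfall. It labels the 101 correctly as screened, calls the trial exploratory and warns of a small sample, and the 37 is printed plainly in the Recruitment section. These caveats temper the charge, but none says that 86 will be missed or qualifies the 80% power.

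Fifth, no passage plans to read non-significance as equivalence. That is true; the risk lies in later interpretation.

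Finally, one might go further and ask for the t2 difference to be made the headline result. That is a separate endpoint question. The Limitations section already treats t2 as the main primary endpoint and leaves the final statistical decisions to the results report.

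**Conclusion.** The point holds as a mismatch between the stated size and power and the article's own recruitment status and timeline. On those figures, 86 participants and 80% power are very unlikely to be reached. Power for the stated effect is 0.44 at the 37 already randomised and about 0.50 to 0.53 at the 43 to 46 projected for the end of March 2026. The detectable f rises from 0.25 to about 0.39 and to about 0.345 to 0.357 respectively.

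This rests on a constant accrual rate, equal arms, no dropout and the between-factors test on which the trial was sized. The interval widths also rest on baseline adjustment with rho = 0.5. Dropout would lower the power further. It should be corrected, because a reader would otherwise credit the trial with a property that its own timeline does not give it.

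**What to change.** - Keep 86 in the Sample Size section as the planned size, with its assumptions.
- Next to it, state the number actually randomised and that the target is not expected to be met. Give the power or detectable effect and the expected 95% CI half-width at that number. On present figures these are power 0.44, detectable f 0.39 and about 0.58 SD at 37; and power 0.50 to 0.53, detectable f about 0.345 to 0.357 and 0.52 to 0.53 SD at 43 to 46.
- In the abstract, report the 37 randomised beside the 101 screened.
- Replace the March 2026 date, which precedes the current version, with the actual status of recruitment and reporting.
- State that a non-significant difference will not be reported as equal efficacy of the two formats.

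The cost is a less favourable stated figure and a few sentences. No extra enrolment and no change of endpoint is needed.

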### Protocol Version History

The study’s design has been registered, and protocol version 1 was prepared and submitted to the journal before the start of the participants’ recruitment. The review process has encountered significant delays—16 months for the first decision postreviews and an additional 3 months postrevisions before the manuscript was withdrawn and resubmitted to JMIR. This resulted in the protocol not being published before the end of the study. However, this protocol version 1.3 does not include any changes to planned study procedures and analysis from protocol version 1 submitted before the start of the study, and the only revisions made to the protocol were more detailed information and explanations of the mentioned procedures and plans. No changes to the analysis plans in the protocol were made after the start of data analysis. One change was made in the registration and protocol at the beginning of the study—the inclusion criteria were changed from young adults in bachelor’s studies to young adults pursuing higher education. Explanations of the main changes in different revisions of the protocol are shown in Textbox 1.

Textbox 1.Protocol version changes.
**Version 1 (January 25, 2024)**
**Version 1.1 (July 31, 2025):** More detailed information on recruitment strategies, plans to promote participant retention, supervision, protocol amendment communication, an explanation of why no interim analysis or data monitoring committee is planned, and some theoretical introduction revisions.**Version 1.2 (December 15, 2025):** Protocol version 1.1 is reworked to the format required by the journal. The content of the protocol is not changed from protocol version 1.1.**Version 1.3 (July 3, 2026):** No major changes to the plan of the study, but some of the details are more clearly stated, for example, discontinuation of the VR sessions if participants state significant discomfort for any reason, not only because of the exposure distress; explicitly stating the study is a superiority trial; clarifying which measure of presence and program engagement is used, and that they will be used for secondary and descriptive analysis. The analysis plan was not changed at this point, except for some more explicit clarifications.

## Discussion

### The Importance of Different Formats

This study will aim to test whether 1-session VR exposure effectiveness for public speaking anxiety differs from the same amount of exposure tasks divided into 3 sessions over the period of 2 weeks, while both programs include 4 weeks of online intervention after the exposure sessions. We consider this study to address an important and practical question regarding the optimal arrangement of VR exposure therapy delivery for public speaking anxiety. A few previous studies found that one VR exposure session [25,43] and 4 sessions of VR exposure therapy [42] were effective in reducing public speaking anxiety. However, to our knowledge, no previous study directly compared the same exposure tasks performed in 1 session and divided into 3 sessions in the context of VR exposure for public speaking anxiety. One session of exposure therapy might be convenient in some contexts but also might be too intensive and long for traditional therapy settings. Extended VR usage in a short period of time might also introduce additional disadvantages in a 1-session exposure. On the other hand, 1-session exposure therapy might be convenient in some contexts, where the number of possible appointments is limited. In addition, the chances of discontinued treatment are likely to be higher in multiple VR exposure sessions compared to one session. This study will compare exposure tasks divided into 3 shorter sessions and a 1-session VR exposure treatment. The study will test an understudied and clinically important question that could generate preliminary evidence of 1-session versus 3-session VR exposure for public speaking comparison and would have the potential to inform future research into optimizing VR exposure for public speaking. However, given a quite limited and specific sample, results would have to be confirmed in larger and more diverse samples.

### Limitations

There are several limitations and risks that we anticipate during the trial. First of all, exposure therapy, by the nature of the method, induces anxiety and discomfort. Participants might be more reluctant to participate in the study and drop out after one exposure session. There will be a need to evaluate the discomfort level of the participant and encourage continuation of the exposure even when they experience discomfort; however, in severe cases of negative reactions, exposure will be discontinued. Another problem we anticipate is participants’ reluctance to continue a transition to in vivo exposure during 4 weeks of online intervention. Low compliance was reported in the equivalent program after VR exposure in the previous study by Lindner et al [43]. To increase compliance, we will ask participants to confirm they will be able to participate in the 4-week online program after the exposure by emphasizing the importance and rationale of online intervention during the in-person session. Another limitation is that although we will measure presence and hypothesized that the length of the sessions might be related to cybersickness for some, for a more parsimonious design of the study, other than excluding participants who reported a history of strong motion sickness, we will not explicitly measure and test motion sickness during VR exposure sessions, which could be one of the confounders of the exposure effectiveness between the different conditions. Due to a very specific and convenient sampling strategy in this research, generalization of the obtained results is strictly limited to young adults pursuing higher education and cannot be directly applied to clinical populations or people from other age groups or social categories. Yet another limitation is that this research focuses on the comparison of different delivery methods with the same amount of VR exposure followed by an online program. Since it does not include a control group that does not have an active intervention, this research is not testing whether this VR exposure therapy is more effective than no treatment, treatment as usual, or a stand-alone online program, but explores comparative efficacy.

Another limitation is that the original protocol version did not detail some of the statistical analysis plans such as handling of sphericity/normality violations, missing data, and multiple imputation model variables, and correction for multiple comparisons. Repeated measures ANOVA might not be the most suitable analysis for the study questions, and a more robust method such as linear mixed effects modeling could be a more appropriate statistical analysis. Moreover, the initially planned multiple primary endpoints have been deemed complicated; thus, *t*_2_ (ie, outcome assessment 1 week after completion of face-to-face VR exposure intervention, either after one 3-hour session or after three 1-hour sessions) is now being considered as the main primary endpoint because the assessment is performed following different conditions, while *t*_7_ remains an additional primary endpoint. We could not add these to the protocol’s statistical analysis plan because this was pointed out by the reviewers after the research team had already seen and worked with the data. These final statistical decisions, including considerations to include more robust analysis methods, will be described in the reports of the study results.

### Conclusions

This protocol details the study that will explore whether a 3-session exposure treatment differs in efficacy from a 1-session treatment for VR exposure–based treatment of public speaking anxiety. This question has relevance in research and practice and could provide preliminary evidence for comparison of different VR exposure for public speaking spacing and scheduling efficacy that could inform future larger confirmatory trials.
